## Abstract

**Introduction:**

Radiogenomic analysis of patients being considered for liver resection is seldom performed in the clinic despite recent evidence indicating that quantitative MRI could improve posthepatectomy outcomes. Meanwhile, the increasingly accessible results from whole genome sequencing reporting on clinically actionable genetic biomarkers are yet to be fully integrated into the clinical care pathway.

**Methods and analysis:**

A prospective observational cohort study of up to 200 participants is planned, recruiting adults with primary or secondary liver cancer being considered for liver resection at Hampshire Hospitals NHS Foundation Trust. The data will be evaluated to address the primary endpoint to calculate the proportion of participants in which the results from whole genome sequencing would have resulted in a change in clinical management. Participants will be offered an additional non-invasive quantitative MRI scan prior to the operation and the impact of the imaging results on treatment decision-making will be evaluated.

**Ethics and dissemination:**

This study was reviewed by the NHS Health Research Authority and given favourable opinion by the Brighton and Sussex Research Ethics Committee (REC reference: 20/PR/0222). Research findings will be discussed with a patient and public involvement and engagement group, presented at relevant scientific conferences and published in open access journals.

**Trial registration number:**

NCT04597710

Strengths and limitations of this studyPrecision1 will be the first study examining the clinical utility of radiogenomic information during the surgical treatment planning stage for patients with primary and secondary liver cancer.Our prospective study is designed to allow us to understand the extent to which quantitative MRI of the liver impacts surgical treatment planning.The additional value of whole genome sequencing will be evaluated to help us identify the presence of any clinically actionable genetic biomarkers which may support precision medicine provision to patients.All patients being considered for liver resection may be eligible for the study, regardless of tumour type or clinical background.The primary limitation of this study is the omission of a tightly matched negative control group where the impact of quantitative imaging on improving patient outcomes could be rigorously examined.

## Introduction

The incidence of treatable liver tumours is on the rise globally, driven by obesity, viral hepatitis and metastases from colorectal cancers. Survival rates can be improved with optimised allocation of treatment options including surgical resection, radiofrequency ablation, embolisation, chemotherapy and targeted molecular therapies (including immunotherapy). The key motivation of this study is to help patients access the most suitable treatment combinations by integrating radiogenomic^1^ and clinical data.

A similar integrated approach, integrating radiology and pathology, has been shown to improve outcomes in breast cancer care.^2^ Detailed pathological analysis of the surgical specimen from breast carcinoma biopsy provides valuable feedback to the radiologist, establishes the completeness of surgical intervention and generates predictive information for therapeutic decisions.^3^

Whole genome sequencing (WGS) has revealed cancer driver mutations and the complex molecular profile of liver cancer.^4^ In many metastatic solid tumours, WGS has been used to identify a significant patient population (31%) who present with a biomarker that predicts sensitivity to a drug and lack any known resistance biomarkers for the same drug.^5^ Identifying which patients possess genomic variants that predict drug response or resistance will allow clinicians to make the optimal treatment decisions. The next technological challenge is integrating WGS into scalable clinical practice.

In addition to the molecular profile of the patient’s liver cancer, a non-invasive assessment of the overall health of the liver using quantitative MRI will be carried out in this study. The MRI metrics from Liver*MultiScan* can quantify changes to liver tissue characteristics, including fibro-inflammation and fat, with the accuracy and reproducibility of the results demonstrated in a number of studies.^6–8^ A recent Innovate UK grant supported Perspectum, Hampshire Hospitals NHS Foundation Trust (HHFT) and University of Edinburgh to assess the use of quantitative MRI in decision support for liver resection. This prospective 143 patient study showed quantitative MRI using Hepatica (which incorporates Liver*MultiScan*) can predict length of patient stay.^9–11^ Patients with liver cancer plus often undiagnosed chronic liver disease performed worse than those with healthy native livers; they also recovered more slowly, costing an extra 1.5 days of hospital stay per patient, a significant clinical impact.

The gold standard of liver assessment relies on imaging and biopsies. Advances in quantitative algorithms provide richer data about the cellular changes associated with liver disease, and greater insight into disease monitoring and treatment efficacy from MRI and digital pathology. In this project, by additionally analysing the genome of both tumour and germline, we aim to understand which variants are driving tumour growth and potentially amenable to targeted therapies and impacting treatment response, along with variants associated with response to surgery and liver regeneration.

In the previous work, we have demonstrated the ability to combine MRI, liver histopathology and circulating (enzyme) biomarkers to improve patient stratification and management.^7^ The innovation in this project is to extend this technology to include discoveries from WGS and integrate them with quantitative MRI and histopathology data to produce a software product for clinical deployment to inform the management of patients with liver tumours. This approach would provide clinicians with a ‘micro to macro’ approach to cancer management, identifying genetic variants associated with tumour pathology, liver function and treatment efficacy, along with their association with pathological and radiological features that can be readily characterised in routine clinical practice. The complementarity of imaging with WGS will be captured by evaluating the current state of the liver from imaging and the future potential of the liver tissue to impact postoperative recovery such as genetic markers for reduced liver regeneration.

## Methods and analysis

### Study design

A prospective observational cohort study.

### Study objectives and endpoints

#### Primary objective

To determine the utility of WGS to aid clinical decision-making in patients referred for liver resection.

#### Secondary objectives

To determine the utility of quantitative multiparametric MRI with Liver*MultiScan* to aid clinical decision-making in patients referred for liver resection.To compare computationally derived digital pathology results with human pathologist assessments of the tumour and non-tumour tissues.To compare the histopathological assessments of liver fat and fibro-inflammation with quantitative MRI metrics (cT1, proton density fat fraction (PDFF)).To evaluate the long-term outcomes and recurrence rates and recurrence patterns of patients as it relates to imaging and WGS.To evaluate whether WGS enables better stratification of patients prior to surgery.

#### Primary endpoint

Proportion of patients for whom clinically actionable data are provided by WGS at the time of surgery. This will be evaluated retrospectively, with clinically actionable data defined as data which would result in a clinician choosing a different medical intervention to the current standard of care.

#### Secondary endpoints

Proportion of patients for whom clinically actionable data are provided by Liver*MultiScan*.Correlation of computationally derived digital pathology results with human pathologist assessments of the tumour and non-tumour tissues, along with assessment of intrarater and inter-rater variability.Correlation of MR measurements of steatosis and fibro-inflammation with digital pathology and human pathology.Performance of WGS and Liver*MultiScan* for predicting postsurgery length of stay in hospital, postoperative liver function, 1-year mortality and recurrence rates.Proportion of patients for whom actionable biomarkers of drug sensitivity are identified with WGS.

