### Digital pathology

Tissue explant samples will be analysed by the clinical histopathologist, and relevant information will be noted. Glass slides will be scanned and analysed using digital pathology methods to evaluate the objective scores of fibrosis, inflammation, ballooning and steatosis.

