### Statistical analysis plan

The data will be evaluated to address the primary endpoint to calculate the proportion of patients in which the results from WGS would have resulted in a change in clinical management. The change in intended management after WGS results will be modelled as a binary variable on the basis of a binomial distribution.

From the literature, we estimate a prevalence of actionable biomarkers derived from genetics of 31%. Using a 5% allowable margin of error and 95% CI, a sample of 200 is required to give a reliable sample to achieve a change in management of 25% of patients.

Descriptive statistics will be reported for all endpoints specified and any interim analyses. Normality of the data will be determined by use of the Shapiro-Wilk test and visual study of histograms. Results will be expressed as mean with SD for continuous normally distributed variables, as median and IQR for non-normally distributed data and as counts and/or percentages for categorical variables. Linearity of continuous data will be assessed by scatter plots. To explore any potential systematic biases, categorical and demographic characteristics expressed as number (%) will be compared using χ^2^. For all tests, a p<0.05 will indicate statistical significance.

Correlations between results from Liver*MultiScan*/Hepatica-derived quantitative MRI metrics and histological features, as well as results from Liver*MultiScan* and genomic features will be determined with Spearman’s rank correlation coefficient and diagnostic performance will be assessed by the calculation of the receiver operating characteristic curve and the determination of the area under the receiver operating characteristic curve with 95% CIs. For all tests, a p<0.05 will be taken to indicate statistical significance.

To explore the impact of genetic variants associated with liver disease, the liver MR-derived biomarkers in those with and without known genetic variants associated with liver disease will be compared using a paired t-test (or non-parametric alternative).

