Radiogenomic exploratory analysis will also be conducted to examine the correlations between image-derived biomarkers, genetic markers of organ damage or tumour malignancy. Digital pathology and circulation blood-derived biomarkers of the disease will be explored with Spearman’s r (rs), with pairwise comparison conducted using two-sided Kolmogorov-Smirnov tests. Listwise deletion will be employed per analysis to included data sets with complete cases for all parameters in the model.

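### The digital-versus-human pathology endpoint rests on correlation, which by itself cannot show systematic over- or under-scoring; an agreement measure should be added

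*Protocol article*

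**What the plan says.** All references are to the Protocol article.

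- **Secondary objectives:** "To compare computationally derived digital pathology results with human pathologist assessments of the tumour and non-tumour tissues".
- **Secondary endpoints:** "Correlation of computationally derived digital pathology results with human pathologist assessments of the tumour and non-tumour tissues", and in the same sentence "along with assessment of intrarater and inter-rater variability". The endpoint does not name a coefficient, a statistic for rater variability, or the raters.
- **Digital pathology:** the clinical histopathologist analyses the explant samples. Separately, slides are scanned and "analysed using digital pathology methods to evaluate the objective scores of fibrosis, inflammation, ballooning and steatosis". No scale is given for either assessment, and the features that the human reader scores are not listed.
- **Statistical analysis plan:** Spearman and ROC analysis are given in the sentence on "quantitative MRI metrics and histological features, as well as results from" the MRI product and genomic features. The exploratory radiogenomic paragraph adds that "Digital pathology and circulation blood-derived biomarkers of the disease will be explored with Spearman"'s coefficient, with two-sided Kolmogorov-Smirnov tests for pairwise comparisons whose pairs are not named. Descriptive statistics are promised for every endpoint.

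**The concern.** Comparing a computed score with a pathologist's assessment is a method-comparison question. It asks whether the two rank patients alike and also whether one reads systematically higher or lower than the other. Correlation addresses only the first part. A constant offset or a stretched scale leaves it unchanged.

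The endpoint itself fixes correlation for this pair, so a fuller analysis plan would be expected to implement correlation. The Introduction says that the project aims at a software product for clinical deployment that combines sequencing, MRI and histopathology data. A digital score that is consistently too high or too low could do well on this endpoint with its bias unmeasured.

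**Working it through.** The article gives no target correlation, agreement limit or power for this endpoint, so there is no figure of the plan to reproduce. The check is whether correlation responds to systematic mis-scoring, and whether any other analysis named in the plan would fill the gap.

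**1. Ordinal illustration (assumed, not from the article).** Human grade x takes the values 0, 1, 2, 3 in proportions 0.4, 0.3, 0.2, 0.1. Digital grade y is one grade higher, capped at 3, so the pairs (x, y) are (0,1), (1,2), (2,3), (3,3).

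- Exact agreement: only (3,3) matches, so 10%.
- Human: mean = 0.3 + 0.4 + 0.3 = 1.0; E[x²] = 0.3 + 0.8 + 0.9 = 2.0; variance = 2.0 − 1.0² = 1.0.
- Digital: mean = 0.4×1 + 0.3×2 + 0.3×3 = 1.9; E[y²] = 0.4 + 1.2 + 2.7 = 4.3; variance = 4.3 − 1.9² = 0.69.
- Covariance: E[xy] = 0.3×2 + 0.2×6 + 0.1×9 = 2.7; 2.7 − 1.0×1.9 = 0.8.
- Quadratic-weighted kappa = 2·cov / (var x + var y + (mean difference)²) = 1.6 / (1.0 + 0.69 + 0.81) = 1.6 / 2.5 = **0.64**.
- Spearman, from mid-ranks as fractions of the sample: human 0.20, 0.55, 0.80, 0.95; digital 0.20, 0.55, 0.85, 0.85; both have mean 0.5. Rank variances are 0.0750 (human) and 0.0735 (digital), and the rank covariance is 0.0735. Spearman = 0.0735 / √(0.0750 × 0.0735) = √0.98 = **0.99**.

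If the scale had a further grade, so that no cap applied, Spearman would be 1.00, exact agreement 0%, and quadratic-weighted kappa 2/(1 + 1 + 1) = 0.67.

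**2. Continuous illustration (simulated).** There were 1,000 replicates of n = 200, the article's maximum sample. True score T ~ N(0,1); human = T + error; digital = shift + scale × (T + error); error SD 0.35. The shift, scale and error SD are assumptions. Entries are averages over replicates; the last column is the share of replicates with p < 0.05.

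| Shift (SD of T) | Scale | Spearman | Lin's CCC | ICC, absolute agreement | ICC, consistency | Mean difference | KS rejects |
|---|---|---|---|---|---|---|---|
| 0 | 1 | 0.88 | 0.89 | 0.89 | 0.89 | 0.00 | 0% |
| 0.25 | 1 | 0.88 | 0.87 | 0.87 | 0.89 | 0.25 | 40% |
| 0.5 | 1 | 0.88 | 0.80 | 0.80 | 0.89 | 0.50 | 100% |
| 1 | 1 | 0.88 | 0.61 | 0.62 | 0.89 | 1.00 | 100% |
| 0 | 2 | 0.88 | 0.71 | 0.71 | 0.71 | 0.00 | 100% |

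Pearson correlation stayed at 0.89 throughout, so the result does not depend on which coefficient is meant.

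**3. Would another named analysis show the bias?**

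- *Rater variability.* If this means variability within and between human readers, it says nothing about digital-versus-human bias. If the algorithm counts as a rater, an absolute-agreement ICC would show a 1 SD shift (0.89 to 0.62), but a consistency ICC would not (0.89 throughout). The text settles neither point.
- *Kolmogorov-Smirnov.* The article does not apply it to this pair. If it were applied, it would flag the larger shifts but only about 40% of the 0.25 SD ones. It ignores the pairing and does not quantify the bias.
- *Descriptive statistics.* If both scores were summarised on one scale, the ordinal case would show means of 1.0 and 1.9. That is a visible difference, but not a paired estimate with limits.

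**The case against.** Much can fairly be said for the plan.

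- **The endpoint has two parts.** Rater variability is an agreement question, and an unnamed statistic for it is a detail that an article commonly leaves to the full plan. This stands: the missing name is no fault. What remains is that the digital-versus-human part is given as correlation.
- **Spearman is not assigned to this pair.** A reader might infer that the analysis section commits to it. It does not. The main analysis text concerns MRI against histology and genomics. The sentence naming digital pathology is exploratory and does not mention human pathology.
- **Other tools are named.** A reader might infer that Spearman and Kolmogorov-Smirnov are the only methods for pathology data. ROC analysis is also given for MRI against histology, and descriptive statistics cover all endpoints. So the documents do not support saying that a biased score would be reported as perfect, because side-by-side summaries might expose it.
- **A common scale, or even the same slides and features, is not stated.** If digital output is continuous and human grading ordinal, rank association is a reasonable measure, and kappa, Bland-Altman and absolute ICC do not apply directly. This stands and limits the remedy to scores on a shared scale.
- **The objective is to compare, not to demonstrate interchangeability**, and no decision rule ties this endpoint to adopting a tool. This stands and limits the consequence.

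**Conclusion.** The point holds in a limited form. The endpoint fixes correlation as the digital-versus-human measure, and the article names no bias or absolute-agreement measure for that pair. Correlation cannot by itself answer the objective. To say that it cannot answer it at all would go too far, since it covers the association part.

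In the assumed ordinal case, Spearman of 0.99 coexists with 10% exact agreement and kappa of 0.64. In the assumed continuous case, Spearman stays at 0.88 while Lin's CCC falls from 0.89 to 0.61 at a 1 SD shift. The sizes depend on the assumed grades, shifts and error. The insensitivity of correlation to a constant or proportional difference does not. The point matters where both methods report on a common scale. It concerns one secondary endpoint and should be corrected, but it does not touch the primary endpoint or the sample size.

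**What to change.** Amend the secondary endpoint so that, where digital and human scores share a scale, it includes:

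- for ordinal grades, quadratic-weighted kappa with 95% CI and percentage exact agreement;
- for continuous scores, Bland-Altman bias and limits of agreement, or an absolute-agreement ICC.

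Use absolute agreement for intrarater and inter-rater variability, and state whether the algorithm counts as a rater. Keep Spearman as a supportive measure and for pairs on different scales, such as MRI metrics against histology.

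The cost is a change of wording and slight extra analysis of data already planned for collection.

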### Clinical assessment

Minimal medical history data will be collected including information regarding previous diagnosis of liver cancer, cirrhosis and comorbidities including chronic kidney disease and diabetes. Information about alcohol consumption, smoking and coffee intake will be collected. Information about any recent chemotherapy regimens will be collected.

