### Whole genome sequencing

Genetic information from tumour tissue and from participant blood sample will be examined. A case review of all participants will be performed with these data to evaluate the clinically actionable information and what steps would have been taken by the clinical care team if this information were available prior to the operation.

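### The secondary endpoint for drug-sensitivity biomarkers is a total yield, so by itself it cannot show the additional value of WGS

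*Protocol article*

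**What the plan says.** Under Secondary endpoints, the protocol article defines the last endpoint as the "Proportion of patients for whom actionable biomarkers of drug sensitivity are identified with WGS". No reference test, earlier result or standard-of-care condition is attached to it.

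The strengths and limitations list, placed after the abstract, states a wider aim: "The additional value of whole genome sequencing will be evaluated to help us identify the presence of any clinically actionable genetic biomarkers". It does not say which endpoint will measure this.

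The primary endpoint is built differently. It counts "data which would result in a clinician choosing a different medical intervention to the current standard of care". Under Whole genome sequencing, a case review of all participants asks "what steps would have been taken by the clinical care team if this information were available prior to the operation". The Statistical analysis plan section adds: "The change in intended management after WGS results will be modelled as a binary variable on the basis of a binomial distribution".

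On data collection, the Clinical assessment section says: "Minimal medical history data will be collected including information regarding previous diagnosis of liver cancer, cirrhosis and comorbidities". It goes on to lifestyle items and recent chemotherapy. The Blood tests section lists routine bloods and serum tumour markers. Neither section names an earlier molecular result on the tumour.

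**The concern.** Additional value is a comparison between what is known with WGS and what was known without it. The drug-sensitivity endpoint contains only the first half. A biomarker that the care team already had on file counts exactly as much as one that WGS brought to light.

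The plan applies a comparison elsewhere. The primary endpoint is set against standard of care, and the imaging assessment notes the surgical plan before and after the surgeon sees the quantitative MRI report. The drug-sensitivity endpoint is the one for which a simple percentage is likely to be quoted, and it has no such anchor.

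Earlier results are plausible in this population. The inclusion criteria admit secondary as well as primary liver cancer, and recent chemotherapy is recorded, so some participants will have had their cancer worked up before entry. If some of them also had molecular results, the reported proportion would credit WGS with findings that it only repeated.

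**Working it through.** **Inputs**

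- Planning prevalence, Statistical analysis plan section: "From the literature, we estimate a prevalence of actionable biomarkers derived from genetics of 31" per cent.
- Origin of that figure, Introduction: "a significant patient population (31%) who present with a biomarker that predicts sensitivity to a drug", with the further condition of no known resistance biomarker for the same drug. It is not described as net of earlier testing.
- N = 200, which the article gives as an upper limit.
- f, the share of biomarker-positive patients whose actionable biomarkers were all known before WGS. The document gives no value, so it is treated as an assumption over the full range 0 to 1.

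**The plan's own figure.** The article gives no expected value for this endpoint. The nearest is the 31%, which corresponds to 0.31 × 200 = 62 positive patients if all 200 are recruited and sequenced.

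**Formula.** New yield = 31% × (1 − f). Excess of total over new yield = 31% × f.

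| f | New yield | Excess (percentage points) | Positives not new, of 62 |
|---|---|---|---|
| 0 | 31.0% | 0 | 0 |
| 10% | 27.9% | 3.1 | about 6 |
| 25% | 23.3% | 7.8 | 15 to 16 |
| 50% | 15.5% | 15.5 | 31 |
| 75% | 7.8% | 23.3 | 46 to 47 |
| 100% | 0% | 31.0 | 62 |

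**Comparison with sampling error.** The 95% half-width around 31% with 200 patients is 1.96 × √(0.31 × 0.69 / 200) = 6.4 percentage points. The excess passes this when 0.31 × f > 0.064, that is, when f is above about 21%. Below that, the excess is smaller than the half-width of the interval. Above it, the confidence interval printed beside the total yield would understate the uncertainty about what WGS added. (The half-width also exceeds the 5% margin stated for the sample size. That is a separate matter, and this point does not depend on it.)

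**Does the primary endpoint share the problem?** A biomarker already known and already acted on in standard care gives no reason to choose a different intervention, so it does not count there. The primary endpoint is therefore largely protected. It measures changes of intervention, however, and does not turn the secondary proportion into a count of new findings.

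**The case against.** The strongest reply is that the two-part design is reasonable. The incremental question belongs to the primary endpoint, and a total yield is a legitimate secondary measure that can be set beside the 31% from the literature. Nothing in the objectives, the endpoints or the Statistical analysis plan section says that the secondary proportion will be presented as additional value. This stands as far as it goes: a total yield is not an error in itself. But the strengths and limitations list ties additional value to the presence of actionable biomarkers, and this endpoint is the one that counts biomarkers. The misreading is easy to make, and the endpoint's wording does nothing to prevent it.

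A reader might infer more: that the endpoint does include biomarkers known from routine testing, and that the value of WGS is therefore overstated. The document does not support this. It describes no routine molecular testing and gives no overlap with WGS, so f may be zero.

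A reader might also infer that known and new findings cannot be separated because earlier results go uncollected. That does not follow either. The medical history sentence introduces an open list in a condensed article, and the full protocol may name more items.

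The size is also only illustrative. The 31% carries a no-resistance condition that the endpoint does not state, and 200 is a maximum. The table shows the range of consequences and is not an estimate.

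**Conclusion.** The point holds in limited form. As worded, the endpoint is a total yield and cannot alone support a statement about what WGS adds in identifying actionable biomarkers. It may overstate that contribution by 31% × f: nothing at f = 0, 7.8 percentage points at f = 25% and 15.5 at f = 50%. These figures assume that the planning prevalence applies to this endpoint and that 200 patients are sequenced. The value of f is unknown. The primary result and the sample size are not affected. The change is a worthwhile and inexpensive improvement to what one secondary endpoint can show.

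**What to change.** Keep the endpoint and label it as the total yield of WGS. Add one data item: any earlier molecular result for the same cancer, taken from existing medical records and entered before the WGS report is opened, with a code for no earlier testing found. The order matters, because a search made after the report is known can be steered by it.

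Then report, on the same denominator as the total yield, the proportion of patients whose actionable drug-sensitivity biomarkers were all already known and the proportion with at least one that is new from WGS. The two add up to the total. Give the new-from-WGS proportion its own 95% confidence interval, and use only that proportion as evidence of additional value.

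The cost is one item abstracted from records and an extra line or two in the results table. Recruitment, study procedures and participant burden do not change. The headline figure may become less favourable. If no participant has an earlier result, the split will show that, and the total yield can then be read as new.
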